#### Recruitment {15}

Potential participants with GPCI will be recruited from the Hospital of Chengdu University of TCM (Sichuan, China), MianYang Hospital of TCM (Sichuan, China) and The Second People’s Hospital of Chengdu PiDu District (Sichuan, China). Our research will use the Internet, hospital announcements, and posters to provide a hotline to call for potential volunteers. If the patients are interested in our study, they will be told of the purpose and content of research as well as the benefits and drawbacks of participating in detail. After screening, the participants meeting the inclusion criteria will be enrolled. The study flow is shown in in the SPIRIT Figure (Fig. 1). Participants will undergo a 6-month treatment period and a 6-month follow-up.

### Assignment of interventions: allocation

#### Sequence generation {16a}

After obtaining the written informed consent from the participants and baseline screening, all eligible patients will be stratified according to early, moderate, and advanced stages of glaucoma [20]: early glaucoma patients have an early glaucomatous visual field loss defined as an MD ≥ − 6 dB; moderate glaucoma patients have a moderate glaucomatous visual field loss defined as MD ≤ − 6 to ≥ − 12 dB; and advanced glaucoma patients had an advanced glaucomatous visual field loss defined as MD ≤ − 12 to ≥ − 20 dB. Random numbers of 001–216 will be automatically generated by SAS software (whole random numbers). Among them, the random numbers 001–072 are assigned to the early stage, the random numbers 073–144 are assigned to the moderate stage, and the random numbers 145–216 are assigned to the advanced stage. After stratifying, the participants will be randomly assigned to the BJYSP group or control group with a ratio of 1:1. An overview of case distribution of each center, specific measurements, and time points of data collection can be found in the SPIRIT Figure (Fig. 2).

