## Abstract

**Background:**

As an irreversible, intractable disease with vision loss, glaucoma leads to permanent and progressive damage of visual function. Lowering high intraocular pressure (HIOP) is the first choice for treating glaucoma; however, the control of HIOP is not enough to prevent progressive vison loss. Currently, the therapies to treat glaucoma with controlled IOP (GPCI) are unsatisfactory. Chinese medicine is effective for improving visual function in patients with GPCI. Bujing Yishi tablets (BJYSP) have been the standard preparation for treating GPCI in our hospital for decades. However, no rigorous randomized controlled clinical studies have investigated its effects and safety.

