### Trial design {8}

The study is designed as a 6-month, multicenter, stratified trial following the prospective, randomized, open-label, blinded endpoint (PROBE) study. The purpose is to evaluate the safety and effect of BJYSP in patients with GPCI. The clinical study was approved by the Sichuan Regional Ethics Review Committee on Chinese Medicine and Medical Ethics Committee of Affiliated Hospital of Chengdu University of TCM (approval no. 2018KL-040). The study was registered at the Chinese Clinical Trial Registry (ChiCTR1800016431, website: http://www.chictr.org.cn). The study will be strictly conducted according to the principles of the Declaration of Helsinki as well as Good Clinical Practice (GCP) guidelines. The trial will be completed according to the Standard Protocols Items: Recommendations for Intervention Trials (SPIRIT) Checklist.

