## Methods: participants, interventions, and outcomes

### Study setting {9}

Potential participants with GPCI will be recruited from the Hospital of Chengdu University of TCM (Sichuan, China), MianYang Hospital of TCM (Sichuan, China), and The Second People’s Hospital of Chengdu PiDu District (Sichuan, China). Our research will use the Internet, hospital announcements, and posters to provide a hotline to call for potential volunteers. If the patients are interested in our study, they will be told of the purpose and content of research as well as the benefits and drawbacks of participating in detail. After screening, the participants meeting the inclusion criteria will be enrolled. The study flow is shown in in the SPIRIT Figure (Fig. 1). Participants will undergo a 6-month treatment period and a 6-month follow-up period.

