### Data collection and management

#### Plans for assessment and collection of outcomes {18a}

An overview of specific measurements and time points for data collection can be found in the SPIRIT Figure. All data will be recorded in detail in the case report form (CRF) after face-to-face visits or telephone calls to the participants. The same investigator will be responsible for the examination of each patient at each assessment. Baseline measurements, demographics, medical history, and previous medications will be collected at the first visit only. Primary and secondary outcomes and safety indicators will be collected every 8 weeks from baseline until week 24. After training in advance and passing a test, two data entry clerks will recheck the CRF and then independently perform data entry. The statistical package Epidata 3.1 will be used for data entry. The data will then be transferred to the statistical SPSS 21.0 software (SPSS Inc., Chicago, IL, USA) for data analysis.

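### In a three-hospital trial stratified by glaucoma stage only, the stated tests use neither hospital nor stage; this adds no bias but gives away a little precision that a simple model would recover.

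*Protocol article*

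**What the plan says.** The Protocol describes the trial in these words: "The study is designed as a 6-month, multicenter, stratified trial" (Trial design {8}). Study setting {9} and Recruitment {15} name three hospitals.

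Under Sequence generation {16a}, "all eligible patients will be stratified according to early, moderate, and advanced stages of glaucoma". Numbers 001 to 216 are divided by stage alone: "the random numbers 001–072 are assigned to the early stage", and the next two blocks of 72 go to the moderate and advanced stages. Allocation is 1:1 from sealed envelopes. The section mentions centres once, to say that the distribution of cases per centre is in Fig. 2, which is not shown.

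Statistical methods {20a} names a chi-square test for categorical data, an independent t-test for measurements and a rank-sum test for graded data. Baseline characteristics are compared descriptively. Additional analyses {20b} are marked as not applicable.

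On examiners, {18a} says: "The same investigator will be responsible for the examination of each patient at each assessment".

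**The concern.** Hospital is the obvious grouping factor in a multicentre trial, and here it enters neither the allocation nor the analysis. Stage is balanced by design and then dropped from the analysis. Two costs follow.

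- **Hospital.** Arms may be uneven within a hospital by chance. If hospitals differ in how much patients change over six months, that unevenness moves the estimated treatment difference up or down at random.
- **Stage.** If stage predicts change, a test that ignores it keeps between-stage variance in the error term although the design has balanced it away. The interval is then wider than it needs to be.

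Precision and power are at stake, not the validity of the comparison.

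**Working it through.** **Inputs from the Protocol.** 216 patients, so 108 per arm; 72 numbers per stage; three hospitals; two-sided α = 0.05 and power 90% (normal quantiles 1.96 and 1.282).

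**The plan's own figure.** n = ½[(1.96 + 1.282)/(asin√0.67 − asin√0.871)]² = 87.86, as stated, hence 88 per arm. Only the 88 and the 216 are used below.

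**Assumptions.** The text gives neither hospital sizes nor hospital effects. I take equal hospitals of 72 (24 per stage), with 144/36/36 and 108/72/36 as alternatives, and exactly 36:36 within each stage. No blocking is stated, so 36:36 favours the plan.

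**Chance imbalance.** For a hospital with 24 patients per stage, the variance of the number on BJYSP is 24 × ¼ × 48/71 = 4.06 per stage. Over three stages this is 12.2, so the SD is 3.5. Simulation of 40,000 trials gives a 95% range of 29 to 43 out of 72. Some hospital is split 60:40 or worse in 8% of trials. That rises to 22% with 108/72/36 and 36% with 144/36/36.

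**Effect on the comparison.** If one hospital differs by e (in within-hospital SDs) and has D of its 72 patients on BJYSP, the treatment difference shifts by e(2D − 72)/108. The mean shift is 0. For e = 0.5 its SD is 0.5 × 2 × 3.5/108 ≈ 0.03. The within-hospital standard error is √(2/108) = 0.136.

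**Power.** Take a continuous comparison with 88 per arm and 90% power. Equal hospitals give a between-hospital variance v = e² × ⅓ × ⅔. Unadjusted power is Φ(3.242/√(1 + v) − 1.96). For e = 0.5, v = 0.0556, and Φ(3.156 − 1.96) = 0.884.

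| One hospital differs by | Share of variance | SD of shift | 97.5th percentile of shift | Unadjusted power |
|---|---|---|---|---|
| 0.25 SD | 1.4% | 0.016 SD | 0.032 SD | 89.6% |
| 0.5 SD | 5.3% | 0.033 SD | 0.065 SD | 88.4% |
| 1.0 SD | 18.2% | 0.065 SD | 0.13 SD | 83.5% |

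The other two size patterns give nearly the same values (88% at 0.5 SD, 83% at 1.0 SD). A hospital term restores about 90%.

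**One cost, not two.** The shift and the power loss are the same noise. At 0.5 SD, √(0.136² + 0.0325²) = 0.140, and 0.136 × √1.0556 = 0.140. The t-test's standard error already contains the shift.

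**In patients.** If hospital explains a share R² of outcome variance, omitting it is like losing 216 × R² patients: 216 × 0.02 = 4.3 and 216 × 0.10 = 21.6. The range 2–10% is assumed.

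**The case against.** The strongest reply is that the effect is small, that hospital sizes and effects are unknown, and that covariate terms are often settled in an analysis plan, which is not shown. The first two parts stand, and they are why this is a modest point. The third stands only in part, because the Protocol does not merely leave the model open: it names unadjusted two-group tests. If an analysis plan already adds these terms, the Protocol text needs only to be aligned with it. Fig. 2 may show planned cases per hospital, but a quota would not balance the arms within a hospital.

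A reader might infer more than the document supports:

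- **Systematic bias between arms.** Randomisation excludes it; the mean shift is zero.
- **Device or examiner offsets distorting the result.** The continuous outcomes are changes from baseline in the same eye, so a constant offset cancels. Keeping one examiner per patient helps it cancel. Only hospital differences in change remain.
- **Expectation at the lead hospital.** The tablets "have been the standard preparation for treating GPCI in our hospital for decades", and the trial is open-label. But expecting BJYSP to work acts through the assigned arm. That is a treatment-by-hospital difference, which neither balanced lists nor a hospital term would remove.
- **Alarming imbalance rates.** With equal hospitals, some hospital has an arm difference of 8 or more in 57% of simulated trials. In a hospital of 72 that means only 40:32 or worse.

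**Conclusion.** The point holds as a matter of precision. The stated tests ignore both the grouping by hospital and the factor used to stratify. At a hospital difference of 0.25 SD the loss is negligible (90% power becomes 89.6%). At 0.5 SD it is about two percentage points. It becomes material only if one hospital differs by about 1 SD, where power is about 83% and the 97.5th percentile of the chance shift, 0.13 SD, is close to one standard error. These figures rest on assumed hospital sizes and effects and on an exact 36:36 split within stage; simple randomisation would spread the arms more widely. The loss from omitting stage is not quantified, because the document does not say how strongly stage predicts change. The case for acting is that the remedy is nearly free.

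**What to change.** Before database lock, while the statistician is still blind, revise Statistical methods {20a}:

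- Analyse each continuous primary outcome with a linear model for change containing treatment, hospital (two parameters) and stage (two parameters).
- Replace the chi-square test by a Cochran–Mantel–Haenszel test, and the rank-sum test by a van Elteren test, both stratified by hospital and stage. State in advance how sparse strata will be combined: nine strata average 216/9 = 24 patients, but a hospital of 36 would have only about 12 per stage.

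The model uses four extra degrees of freedom (with 216 patients, 214 residual degrees of freedom become 210) and needs no extra patients or measurements. Under {25}, a change to the analyses also means submitting a new protocol version to the ethics committee.

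Leave the envelope lists unchanged. Trial status says that recruitment began in June 2018, and small blocks within nine strata would make assignments easier to predict in an open-label trial.

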#### Concealment mechanism {16b}

Random numbers will be placed in a same shape and size envelope and subsequently sealed for concealing group allocation and to avoid selection bias. The allocation random sequence will be stored and concealed from the investigators, statistician, and outcomes assessors to prevent detection bias.

#### Implementation {16c}

The designated statisticians will generate the allocation sequence, different investigators designated by the project leader will enroll or assign participants.

### Assignment of interventions: blinding

#### Who will be blinded {17a}

In this PROBE design trial, both participants and treating clinicians will be aware of the treatment assignment. Information including BCVA, visual field, VEP, HRT II, IOP, and TCM clinical symptom scales will be assessed by independent assessors who are blind to the assignment and treatment. The principal investigators, statistician, and outcomes assessors will be blind to the treatment assignments until the database is locked.

#### Procedure for unblinding if needed {17b}

Unblinding the investigators will be permissible only in specific situations, such as when knowledge of the actual treatment is highly necessary for the appropriate management of participants (e.g. serious adverse events).

### Data collection and management

#### Plans for assessment and collection of outcomes {18a}

An overview of specific measurements and time points for data collection can be found in the SPIRIT Figure. All data will be recorded in detail in the case report form (CRF) after face-to-face visits or telephone calls to the participants. The same investigator will be responsible for the examination of each patient at each assessment. Baseline measurements, demographics, medical history, and previous medications will be collected at the first visit only. Primary and secondary outcomes and safety indicators will be collected every 8 weeks from baseline until week 24. After training in advance and passing a test, two data entry clerks will recheck the CRF and then independently perform data entry. The statistical package Epidata 3.1 will be used for data entry. The data will then be transferred to the statistical SPSS 21.0 software (SPSS Inc., Chicago, IL, USA) for data analysis.

#### Plans to promote participant retention and complete follow-up {18b}

Frequent follow-up phone call will be conducted to promote participant retention.

#### Data management {19}

After training in advance and passing a test, two data entry clerks will recheck the CRF and then independently perform data entry back to back. The statistical package Epidata 3.1 will be used to check entry consistency and seek out abnormal data in accordance with a pre-set value range automatically. The third person (data manager) independently checks and judges the input data. The principle investigators from each of the trial sites will confirm whether all CRFs have been timely completed, ensure that the withdrawal of participants and all adverse events are documented in CRFs, and so on). All original data and relevant records will be properly classified and stored at each study center under confidential conditions for 3 years.

#### Confidentiality {27}

Participants’ personal information will be kept confidential in the same way as their medical histories in the hospital before, during, and after the trial.

#### Plans for collection, laboratory evaluation, and storage of biological specimens for genetic or molecular analysis in this trial/future use {33}

Not applicable.

### Statistical methods

#### Statistical methods for primary and secondary outcomes {20a}

Statisticians will independently undertake statistical analysis. All data will be presented as the means ± standard deviation (SD). Statistical analysis will be performed by SPSS 21.0 software (SPSS Inc., Chicago, IL, USA). All statistical tests will be two-sided tests, and the statistical significance threshold will be set at *P* < 0.05. The chi-square test will be used for categorical variables, an independent Student’s t-test will be used on measurement data, and rank-sum test will be used for grade data. To assess covariate balance, baseline characteristics will be summarized and compared between the BJYSP group and the control group by means of simple descriptive statistics.

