#### Outcomes {12}

##### Primary outcomes

Primary outcomes help us to determine whether visual function is improved and whether BJYSP is effective. They will be as follows: (1) mean change in BCVA in the study eye will be measured at baseline and 2, 4, and 6 months thereafter; (2) mean change in values of the pattern standard deviation (PSD), mean defect (MD), square root of loss variance (sLV) in the study eye, as determined by an Octopus 900 perimeter, at baseline and 2, 4, and 6 months thereafter; (3) mean change in values of the latency of negative response 75 (LN75), amplitude of negative response 75 (AN75), latency of positive response 100 (LP100), and amplitude of positive response 100 (AP100) in the study eye, as determined by VTAS 2000 VEP, at baseline and 2, 4, and 6 months thereafter; and (4) mean change in values of the disk area (DA), cup area (CA), rim area (RA), cup volume (CV), rim volume (RV), cup/disk area ratio (C/DAR), linear cup/disk ratio (C/DLR), mean cup depth (mCD), maximum cup depth (maxCD), cup shape measure (CSM), height variation contour (HVC), mean RNFL thickness (MRNFLT), and RNFL cross-sectional area (RCSA) in the study eye, as determined by Heidelberg retina tomography II (HRT II), at baseline and 2, 4, and 6 months thereafter.

Potential participants will be told in detail of the purpose and content of research as well as the benefits and drawbacks of participating. Informed consent will be obtained by the designee at each site from those willing to participate. The schedule of visits and tests is shown in the SPIRIT Figure (Fig. 2). Participants will be reminded by telephone the week before the study visit by research nurses at each site.

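### The t-test on change adjusts neither for baseline as a covariate nor for the stage strata used in randomisation, so the comparison is valid but less precise than the design allows

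*Protocol article*

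**What the plan says.** All of this is in the protocol article.

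- **Test.** Statistical methods for primary and secondary outcomes {20a} assigns chi-square tests to categorical variables and then states, with the t-test specified as the independent Student's form: "t-test will be used on measurement data, and rank-sum test will be used for grade data". No covariate or stratum appears.
- **Role of baseline in the analysis.** The same section says "baseline characteristics will be summarized and compared between the BJYSP group and the control group by means of simple descriptive statistics". That describes balance; it does not adjust for it.
- **Other analyses.** Methods for additional analyses {20b} is marked as not applicable, so no stage-adjusted or by-stage analysis is stated elsewhere.
- **Outcomes.** The primary outcomes are changes: "mean change in BCVA in the study eye will be measured at baseline and 2, 4, and 6 months thereafter", and for the visual field "mean change in values of the pattern standard deviation (PSD), mean defect (MD), square root of loss variance (sLV) in the study eye". The VEP and HRT II outcomes are defined the same way.
- **Randomisation.** Under Sequence generation {16a}, "all eligible patients will be stratified according to early, moderate, and advanced stages of glaucoma". The strata are cut on baseline MD; the middle one is "moderate glaucomatous visual field loss defined as MD ≤ − 6 to ≥ − 12 dB". Each stage has 72 numbers ("the random numbers 001–072 are assigned to the early stage", and likewise for the other two). Then "After stratifying, the participants will be randomly assigned to the BJYSP group or control group with a ratio of 1:1".
- **Purpose of staging.** Explanation for the choice of comparators {6b} says patients are classified by stage so that the effect can be seen at different severities.

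**The concern.** Stage shapes the randomisation but enters no stated analysis, and the baseline value enters only by subtraction.

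Stratifying keeps stage differences largely out of the treatment contrast. If change differs by stage, an unstratified t-test still counts those differences as error. Separately, a change score gives baseline a fixed coefficient of 1. When baseline and follow-up correlate below 1, that over-corrects a chance baseline difference (regression to the mean) and adds variance that ANCOVA avoids by estimating the coefficient.

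At stake are interval width and power. The article names its test, so this is a choice it makes and not a detail left to an analysis plan.

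**Working it through.** **The plan's own figure.** Sample size {14} uses an arcsine formula for two proportions: ½ × [(1.96 + 1.282) / (arcsin√0.67 − arcsin√0.871)]². The arcsine difference is 0.24457 in size, so 3.242/0.24457 = 13.256, and 13.256²/2 = 87.86 per arm, as stated. It rests on a binary effective rate and supplies no standard deviation, mean difference or correlation for the primary outcomes. What follows must therefore be in relative terms over an assumed range.

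**Step 1: baseline as a covariate.** Let s² be the variance of the outcome, equal at both visits, and r the baseline to month-6 correlation.

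- Change score: variance 2(1 − r)s².
- ANCOVA on baseline: variance (1 − r²)s² = (1 − r)(1 + r)s².
- Ratio ANCOVA/change: (1 + r)/2. The t-test standard error (SE) is larger by the factor √[2/(1 + r)].

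The last column is the power of the t-test on change when ANCOVA has 90%: Φ[(1.96 + 1.2816)/√(2/(1 + r)) − 1.96].

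| r (assumed) | Variance ratio | t-test SE wider by | Power of t-test on change |
|---|---|---|---|
| 0.5 | 0.75 | 15.5% | 80.2% |
| 0.7 | 0.85 | 8.5% | 84.8% |
| 0.9 | 0.95 | 2.6% | 88.5% |
| 0.95 | 0.975 | 1.3% | 89.3% |

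At r = 0.7, 1/0.85 = 1.18, so ANCOVA gives the precision of about 18% more patients.

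**Where MD may fall in that range.** Suppose MD is spread evenly within strata of 0 to −6, −6 to −12 and −12 to −20 dB, with equal numbers in each. The between-stage variance is 28.22 and the mean within-stage variance is 3.78, total 32.0. With an assumed measurement SD of 1.5 dB (variance 2.25), r = 32.0/34.25 = 0.93 and √(2/1.93) = 1.02. Under these assumptions MD sits at the small-gain end, because eligibility spans so wide a range of severity. Other outcomes may differ.

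**Step 2: stage.** Differences in level between stages cancel in a change score. Only the share R² of the variance of change that stage explains matters. If the arms are balanced within stage, the unstratified SE is too large by 1/√(1 − R²), and the nominal 5% test runs at 2[1 − Φ(1.96/√(1 − R²))].

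| R² (assumed) | SE wider by | Actual size of nominal 5% test |
|---|---|---|
| 0% | 0% | 5.0% |
| 5% | 2.6% | 4.4% |
| 10% | 5.4% | 3.9% |
| 20% | 11.8% | 2.8% |

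**Step 3: combining the two.** The losses in steps 1 and 2 should not simply be multiplied. For MD, stage is a coarse version of the baseline value, so a model that already contains baseline MD has captured part of what stage offers.

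**The case against.** The strongest reply is that nothing here is invalid. A two-sample t-test on change in a randomised trial is unbiased and does not exceed its nominal error rate, so preferring ANCOVA is a recommendation on efficiency. That stands.

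A reader might go further and infer that the analysis ignores baseline altogether. The documents do not support that: the primary outcomes are defined as mean changes, so baseline is subtracted. The much larger loss against a t-test on final values (ANCOVA variance 1 − r² = 0.51 of it at r = 0.7) therefore does not apply to them. Nor does chance baseline imbalance stay uncorrected in a change score; what can remain is over-correction through regression to the mean.

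A reader might also infer that the test is conservative as a matter of course. That needs the arms to be near-balanced within each stage. The article states 1:1 allocation after stratifying but does not describe how balance is kept within a stage. If allocation there is simple, the t-test is less efficient but not conservative.

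Finally, an article condenses, and modelling of the repeated visits or of graded outcomes may sit in an analysis plan. That is fair for the repeated visits, and no fault is found on that count. It does not answer the main point, because the article positively names an unadjusted test for a stratified design.

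**Conclusion.** The point holds as one of modest precision. The stated t-test on change does not use baseline as a covariate or the three randomisation strata, and no other stated analysis does.

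The SE is wider than under ANCOVA on baseline by about 15.5% to 2.6% for r from 0.5 to 0.9. Any further loss from omitting stage depends on how far stage predicts change, and it partly overlaps with the baseline gain for MD. The figures rest on assumed correlations, assumed variance shares and equal variances at the two visits, so the direction is firmer than the size.

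For the graded TCM symptoms, the named rank-sum test likewise carries no term for baseline grade or stage.

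**What to change.** Before database lock and unblinding:

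- For continuous outcomes, replace the t-test with ANCOVA, or a repeated-measures equivalent, with treatment, baseline value of the outcome and three-level stage as terms. Report the adjusted difference with its 95% confidence interval.
- For graded TCM symptoms, use a stage-stratified rank test (van Elteren).
- For proportions, use Cochran-Mantel-Haenszel stratified by stage.

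Baseline values and stage are already scheduled for collection, so no new measurement or patient is needed; the model spends only a few degrees of freedom. The cost is a wording amendment. Under the section on protocol amendments {25}, a change to the analyses requires a new protocol version submitted to the ethics committee for approval. The article does not show whether data collection has finished (Trial status gives only an expected end of recruitment), so the amendment should record that it was made before unblinding.
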